### Study measures

The comprehensive assessment in the observational study includes various psychological measures which are widely used in research. Unless otherwise stated, the name of each scale represents the underlying construct measured, with higher scores indicating more severe manifestations of the respective construct. Table 2 gives an overview over the study measures. References for study measures that have previously been published elsewhere are provided in the text (see Additional File 1 for self-constructed study measures).

**Table 2 Tab2:** Study measures

Study Measures	T1	T2
**Psychosocial adjustment**		
DISABKIDS Chronic Generic Module (DCGM-37)	x	x
WHO-5 Well-Being Index (WHO-5)	x	x
Satisfaction with Life Scale (SWLS)	x	x
Self-Assessment Manikin (SAM)	x	x
**Psychosocial adaptation – Resources**		
Questionnaire of Resources in Childhood and Youth (FRKJ 8–16)	x	x
Questionnaire of Social Competence in Children and Adolescents, subscale social initiative (FSK-KJ)	x	x
Berlin Social Support Scales (BSSS), subscale seeking social support	x	x
Self-Control Scale (SCS-K-D)	x	x
Self-Compassion Scale (SCS-D short version)	x	x
Functionality Appreciation Scale (FAS)	x	x
**Psychosocial adaptation – Coping strategies**		
Coping with Chronic Health Conditions Questionnaire (CODI)	x	x
Questionnaire of Stress and Stress Management in Childhood and Adolescence (SSKJ 3–8), subscale problem-oriented coping	x	x
Emotion Regulation Questionnaire (ERQ)	x	x
Cognitive Emotion Regulation Questionnaire (CERQ), subscale positive refocusing	x	x
Benefit Finding Scale for Children (BFSC)	x	x
**Generic risk factors – Psychopathology**		
Patient Health Questionnaire (PHQ-9)	x^a^	x
General Anxiety Disorder-Scale (GAD-7)	x^a^	x
**Generic risk factors – Developmental tasks and stress**		
Questionnaire on Developmental Tasks in Adolescence		x
Questionnaire on critical life events		x
Perceived Stress Scale (PSS-4)		x
Questionnaire on overall impact of the Covid-19 pandemic		x
**Generic risk factors – Sociodemographic and CC-specific information**	x	x^b^

*Note.*^a^Assessed in clinical centres; ^b^Except age at diagnosis

### Assessment of adjustment: HRQoL and well-being

Multiple indicators for the assessment of HRQoL and well-being are used.

#### HRQoL

HRQoL is one of the major outcomes in medical research and is measured by the German version of the DISABKIDS Chronic Generic Module (DCGM-37) [35]. The 37 items are allocated to three domains with two facets each: psychological (independence, emotions), social (social exclusion, social inclusion), and physical (physical limitations, treatment/medication). The items are measured on a 5-point Likert scale ranging from 1 “never” to 5 “always”. A sample item is: “Do you have fun in your life?”. Internal consistency of the subscales ranges from Cronbach’s α = .70 to Cronbach’s α = .87. Internal consistency for the total score is Cronbach’s α = .93 [35].

#### Well-being

The German version of the 5-item WHO-5 Well-Being Index (WHO-5) assesses overall well-being [36]. Children and adolescents are asked to report the presence of positive feelings in the last 2 weeks on a 6-point scale ranging from 1 “at no time” to 6 “all the time” (e.g., “I have felt calm and relaxed.”). The WHO-5 can be validly administered to children and adolescents in pediatric care [37].

#### Satisfaction with life

The German version of the 5-item Satisfaction with Life Scale (SWLS) [38] is used to measure satisfaction with life (e.g., “I am satisfied with my life.”) whereby the first two items are adapted in their wording to the age group. The items are measured on a scale ranging from 1 “low satisfaction” to 7 “high satisfaction”. Internal consistency for the total score is Cronbach’s α = .92 [39].

#### Overall well-being

The Self-Assessment Manikin (SAM) is a picture-based assessment of affective reactions towards different stimuli [40, 41]. The current study focuses on overall well-being. Participants are asked “How do you feel in general?” and have to choose one of the five manikins ranging from looking very unhappy to smiling brightly.

### Assessment of psychosocial adaptation: resources and coping strategies

Multiple indicators for the assessment of psychosocial adaptation are used.

#### Resources in childhood and youth

Seven of the ten subscales of the Questionnaire of Resources in Childhood and Youth (FRKJ 8–16) are used to assess personal (empathy and perspective-taking, self-efficacy, self-esteem, optimism, and sense of coherence) and social resources (parental and social support, peer-group integration) in children and adolescents [42]. Each subscale contains six items. Participants’ responses are measured on a scale ranging from 1 “never true” to 4 “always true”. A sample item is: “When I set my mind to something, I get it done.”. The reliability of the subscales ranges from Cronbach’s α = .69 to Cronbach’s α = .89 [42].

#### Social initiative

The Questionnaire of Social Competence in Children and Adolescents (FSK-KJ) is a multidimensional questionnaire to assess social competencies in children and adolescents [43]. The current study uses the subscale “social initiative” (Cronbach’s α = .83) [43]. The subscale contains eight items with a response format ranging from 1 “not at all applicable” to 5 “absolutely applicable”. A sample item is: “I make friends easily.”.

#### Seeking social support

The Berlin Social Support Scales (BSSS) were developed in the context of coping with illness and measure social support on multiple dimensions [44]. The 5-item subscale “seeking social support” is used whereby participants rate how much the presented statements regarding support seeking apply to them on a scale ranging from 1 “strongly disagree” to 4 “strongly agree” (e.g., “When I have concerns, I seek out a conversation.”). In addition, the source of support is assessed by presenting a list of possible sources of support (e.g., parents, relatives, friends, teachers, etc.). Internal consistency of the total score is Cronbach’s α = .81 [44].

#### Self-control

The German version of the 13-item Self-Control Scale (SCS-K-D, short version) is used to assess dispositional self-regulatory behaviors (e.g., “I am good at resisting temptation.”) [45]. Items are scored on a 5-point Likert scale, ranging from 1 “not at all like me” to 5 “very much like me”. Internal consistency for the total score is Cronbach’s α = .79 [45].

#### Self-compassion

The German version of the Self-Compassion Scale (SCS-D, short version) encompasses 12 items rated on a 5-point scale, ranging from 1 “almost never” to 5 “almost always” [46] and comprises six subscales: self-kindness, self-judgment, common humanity, isolation, mindfulness, over-identification. A sample item is: “I try to be understanding and patient towards those aspects of my personality I don’t like.”. Internal consistency for the subscales ranges from Cronbach’s α = .54 to Cronbach’s α = .75 (total score: Cronbach’s α = .86) [47].

#### Body functionality

The German version of the 7-item Functionality Appreciation Scale (FAS) is used to assess body functionality [48]. Participants indicate their appreciation of body functionality on a 5-point Likert scale ranging from 1 “strongly disagree” to 5 “strongly agree” (e.g., “I appreciate my body for what it is capable of doing.”). Internal consistency for the FAS score is Cronbach’s α = .86 [48].

#### Coping with chronic health conditions

The German version of the 29-item Coping with Chronic Health Conditions Questionnaire (CODI) is used to assess coping strategies of children and adolescents with CCs [49]. The CODI comprises six domains: acceptance, avoidance, cognitive-palliative, distance, emotional reaction, and wishful thinking. Participants indicate their use of the coping strategies on a 5-point Likert scale ranging from 1 “never” to 5 “all the time” (e.g., “I try to ignore my illness.”). Depending on the domain, the internal consistency of the questionnaire ranges from Cronbach’s α = .69 to Cronbach’s α = .83 [49].

#### Problem-solving skills

Problem-solving skills are measured by the 6-item subscale “problem-oriented coping” of the Questionnaire of Stress and Stress Management in Childhood and Adolescence (SSKJ 3–8) [50]. The wording of the instruction was adapted to the specific CC context. Items are scored on a 5-point Likert scale, ranging from 1 “never” to 5 “always”. A sample item is: “I then decide on a way to solve the problem”. The internal consistency for the subscale is Cronbach’s α = 89 [50].

#### Emotion regulation

The German version of the 10-item Emotion Regulation Questionnaire (ERQ) is used to assess the habitual use of two emotion regulation strategies: cognitive reappraisal (6 items) and expressive suppression (4 items) [51]. Items are scored on a 7-point Likert scale, ranging from 1 “strongly disagree” to 7 “strongly agree”. A sample item is: “I keep my emotions to myself”. The subscales of the ERQ show an internal consistency of Cronbach’s α = .76 for the subscale “cognitive reappraisal” and Cronbach’s α = .74 for the subscale “expressive suppression” [51].

#### Positive refocusing

The Cognitive Emotion Regulation Questionnaire (CERQ) consists of nine subscales, each referring to what someone thinks after the experience of threatening or stressful events [52]. This study uses the German version of the 3-item subscale “positive refocusing “(e.g., “I think of pleasant things that have nothing to do with it.”). Participants indicate on a 5-point Likert scale ranging from 1 “(almost) never” to 5 “(almost) always” how much they rely on positive refocusing. The internal consistency of the subscale is Cronbach’s α = .85 [53].

#### Benefit finding

A German version of the 10-item Benefit Finding Scale for Children (BFSC) is used to assess benefit finding [54]. Participants indicate the extent to which their illness has helped them grow personally (e.g., “Has helped me to become a stronger person.”). Their responses are measured on a 5-point scale ranging from 1″ not at all true for me” to 5 “very true for me”. The BFSC has an internal consistency of Cronbach’s α = .83 [54].

### Assessment of psychopathology

Additional instruments were used at T2, including the PHQ-9 and the GAD-7 from the mental health screening in the clinical centres to assess development of mental health of the participants.

#### Depression

The German version of the 9-item Patient Health Questionnaire (PHQ-9) is administered as a screening inventory to detect depressive symptoms within the past 2 weeks (e.g., “Little interest or pleasure in doing things.”) [55]. We omitted one item assessing suicidal ideation. Responses are measured on a 4-point Likert scale ranging from 0 “not at all” to 3 “nearly every day”. The computerized version of the PHQ-9 has an internal consistency of Cronbach’s α = .88 [56].

#### Anxiety

The German version of the General Anxiety Disorder-Scale (GAD-7) is administered to detect symptoms of anxiety within the past 2 weeks (e.g., “Feeling nervous, anxious or on edge.”) [57, 58]. The GAD-7 consists of seven items with a 4-point Likert scale ranging from 0 “not at all” to 3 “nearly every day”. The GAD-7 shows an internal consistency of Cronbach’s α = .79 to Cronbach’s α = .91 [59] and successful usage in adolescents is reported [60, 61].

### Assessment of developmental tasks and stress

Multiple indicators for the assessment of developmental tasks and stress are used.

#### Developmental tasks

A modified version of the Questionnaire on Developmental Tasks in Adolescence is administered to assess normative developmental tasks in youth [62]. For the current study, the questionnaire was shortened to eleven items and the wording was adapted to the targeted age group. Participants indicate their subjective importance of the presented developmental tasks on a 6-point Likert scale ranging from 1 “not (yet) important” to 6 “no longer important” (e.g., become more independent from parents, accepting changes in the body and one’s appearance). Participants also mark on a line where they are in the process of completing each developmental task.

#### Critical life events

A self-constructed 10-item questionnaire assesses critical life events that occurred in participants’ life during the past 12 months (e.g., “Did you move out of your parents’ house?”). If participants select one or more of the events, they are asked to indicate how each of them has impacted their lives on a slider ranging from 0 “not at all” to 100 “completely”. Additionally, an open format question asks for further potential life events not covered by the items presented.

#### Perceived stress

The German version of the 4-item Perceived Stress Scale (PSS-4) is used to assess the frequency of perceived stress in the past 12 months (e.g., “In the last twelve months, how often have you felt that you were unable to control the important things in your life?”) [63]. The items are measured on a 5-point Likert scale ranging from 1 “never” to 5 “very often”. The internal consistency is Cronbach’s α = .72 [63].

#### Overall impact of the Covid-19 pandemic

A self-constructed 4-item Covid-19-specific scale is administered to assess the impact of the Covid-19 pandemic on different life domains: family life, education, interaction with friends and leisure activities. Participants use a slider to indicate how much each of these life domains has changed as a result of the Covid-19 pandemic on a scale ranging from 0 “not at all” to 100 “completely”.

### Sociodemographic and CC-specific information

Sociodemographic information collected in the study comprise gender, age, body size and weight, living situation, and education as self-assessments [64]. Subjective socioeconomic status is assessed by a slightly modified version of the MacArthur Scale [65]. CC-specific variables encompass the CC itself, age at diagnosis, further physical and mental disorders, psychological treatment, subjective severity of the CC, subjective health status using three items that were developed based on widely used measures [66, 67], as well as satisfaction with treatment staff and identification with the group of people who have the same CC [68].

### Covid-19 monitoring

In reaction to the Covid-19 pandemic, the additional online survey contains questions regarding psychosocial adjustment and adaptation as well as risk perception, emotions, psychological distress and the impact of the Covid-19 pandemic. Established instruments, as well as self-constructed Covid-19-specific instruments, are used for this purpose (see Table 3 for an overview and Additional file 2 for detailed information on the Covid-19 specific measures).

**Table 3 Tab3:** Study measures for intermediate Covid-19 study

Study Measures	Covid-19 study
**Psychosocial adjustment**	
WHO-5 Well-Being Index (WHO-5)	x^a^
Satisfaction with Life Scale (SWLS)	x^a^
**Psychosocial adaptation – Resources**	
Questionnaire of Resources in Childhood and Youth (FRKJ 8–16), subscale peer-group integration	x
Berlin Social Support Scales (BSSS), subscale seeking social support	x^b^
**Psychosocial adaptation – Coping strategies**	
Benefit Finding Scale for Children (BFSC)	x^b^
**Covid-19-specific resources**	
Self-efficacy beliefs	x
Outcome expectations	x
Resilience	x
Contact to peers	x
Social norms	x
**Covid-19-specific coping strategies**	
Coping across Situations Questionnaire (CASQ)	x^b^
Preparedness	x
**Risk perception**	x
**Emotions and psychological distress during the Covid-19 pandemic**	
Positive and Negative Affect Schedule (PANAS)	x
Perceived Stress Scale (PSS-4)	x
Emotions	x
**General questions regarding the Covid-19 pandemic**	x
**Overall impact of the Covid-19 pandemic**	x^c^

*Note.*^a^As used in T1 and T2. ^b^Adapted to Covid-19 pandemic situation. ^c^Includes additional items

### Sample size

The sample size for the prospective analysis is determined by the main and most complex analysis applying latent structural equation modeling (SEM). Up to now, there is no unambiguous rule on required sample sizes in SEM, as it is dependent on several aspects (e.g., model complexity, data distribution, amount of missing data, effect size, and number of parameters that have to be computed). As a rule of thumb, the sample size should not be lower than 200 although computations should be possible with sample sizes greater than 100 [69]. As a multi-group latent SEM (grouping factor: mental health status inconspicuous vs. conspicuous) should be applied to the data, a total sample size of 400 should be sufficient. Both the inconspicuous and the conspicuous group should consist of a minimum of 100 participants. Therefore, at least 200 participants in each group should be achieved. However, regarding the prevalence of depression and anxiety in youth with CCs, while considering possible barriers to participate with symptoms of depression and/or anxiety, we expect a higher amount of inconspicuous participants. To reduce bias in estimates obtained, which may occur due to non-random differences in covariates between groups, we will consider appropriate matching procedures. Therefore, we increased the targeted sample size for the inconspicuous group to 250 participants during the recruitment process.

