**Methods/design:**

We plan to consecutively recruit *N* = 450 adolescents (12–21 years) from three German patient registries for chronic conditions (type 1 diabetes, cystic fibrosis, or juvenile idiopathic arthritis). Based on screening for anxiety and depression, adolescents are assigned to two parallel groups – “inconspicuous” (PHQ-9 and GAD-7 < 7) vs. “conspicuous” (PHQ-9 or GAD-7 ≥ 7) – participating in a prospective online survey at baseline and 12-month follow-up. At two time points (T1, T2), we assess (1) intra- and interpersonal resiliency factors, (2) coping strategies, and (3) health-related quality of life, well-being, satisfaction with life, anxiety and depression. Using a cross-lagged panel design, we will examine the bidirectional longitudinal relations between resiliency factors and coping strategies, psychological adaptation, and psychosocial adjustment. To monitor Covid-19 pandemic effects, participants are also invited to take part in an intermediate online survey.

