### Recruitment

Consecutive recruitment for this ongoing trial started in June 2019 in clinical centres. Adolescents with type 1 diabetes, cystic fibrosis, or juvenile idiopathic arthritis are recruited during their regular check-up visits in hospitals, clinics, medical practices, and medical centres across Germany. These clinical institutions all take part in one of the following German patient registries, the National Paediatric Rheumatologic Database (NPRD) [32], the National Diabetes Registry (DPV) [33], or the Cystic Fibrosis (CF) Registry [34]. Eligible patients (and their parents) are informed about the research project by the treating physician at the clinical centre and eligible patients are screened for anxiety and depression. All participants and parents of participants under legal age (< 18 years) provide written informed consent prior to inclusion into the study. Informed consent is sent to the University of Potsdam and all further recruitment activities are conducted by researchers there. In the next step, participants are invited to take part in the prospective online survey, which means that they are contacted by phone and receive an invitation email with the link to the survey. If they do not complete the questionnaire, they are contacted by email and phone at set time intervals and reminded to participate. Furthermore, they receive monthly SMS greetings to increase study adherence. To monitor the Covid-19 pandemic effects, participants are invited to take part in an intermediate online survey. Survey data will be connected with the objective medical background data provided by the patient registries: diagnosis, CC severity, CC duration and CC-specific data, e.g., hemoglobin A1c (HbA1c), forced expiratory volume in 1 s (FEV1), and clinical juvenile arthritis disease activity score (cJADAS). Principles of good research practice, data, and participants’ privacy protection are strictly adhered to. For each successfully recruited participant, the respective clinical unit receives a financial compensation of 75€ for its recruitment effort. Participants receive gift coupons as compensation for their time at T1 (20€) and T2 (30€). The online survey started in August 2019 and has been recruiting participants consecutively since. See Table 1 for preliminary descriptive data on the sample.

**Table 1 Tab1:** Demographics of the preliminary sample

Variables	Total (***n*** = 426)	Inconspicuous (***n*** = 297)	Conspicuous (***n*** = 129)
Gender			

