## Discussion

CCs are quite common among adolescents and can hinder their age-appropriate psychosocial development. So far, research has mainly focused on various risk factors for such an unfavorable development. The present study aims to undertake a paradigm shift in the research on CCs by explicitly focusing on the intrapersonal resources of those affected and a broad range of psychosocial adjustments. The present study aims to examine the reciprocal associations between resiliency and coping strategies (psychosocial adaptation) on the one hand and psychosocial adjustment on the other hand across a one-year period in a sample of adolescents facing CCs. The findings will expand our current knowledge addressing the following aspects: (1) This study focuses on an assessment of resiliency factors and coping strategies in explaining psychosocial adjustment. Up to now, protective factors and their incremental contribution have been rarely addressed but provide unique starting points for preventional and interventional approaches; (2) A major strength is the inclusion and longer-term follow-up of youths in a sensitive developmental stage for the emergence of mental health problems, non-adherence and health-related risk behaviors [22]. Adolescence is considered to be the “cradle of health-related behaviors” and therefore provides great opportunities for maintaining and improving current and future health [22]; (3) The simultaneous consideration of specific CCs differing in various CC-related aspects (e.g., the role of pain; medical treatment or life-expectancy) follows a non-categorical approach [75]. By including CCs with diverse characteristics, one can identify the unique vs. generic characteristics in the process of psychosocial adaptation. Especially the identification of generic modifiable aspects will support the theory-driven development of non-categorical interventions, which is highly important for those adolescents with a rare condition [7]. (4) The broad recruitment via the German patient registries enables a representative sample. (5) We will include both, those adolescents facing problems in coping with their CC and those who are doing well. By ensuring that both subsamples are nearly comparable with respect to the sample size, we will be able to compare their respective resource profiles. In addition, the sample sizes will be large enough for applying multi-group comparisons over time. (6) Using a comprehensive set of instruments, we can assess various aspects of psychosocial adaptation in the face of CCs (e.g., social support, self-compassion, and problem-solving skills). (7) The study takes an interdisciplinary approach: Medical data are linked to psychological parameters, thus allowing deeper insights into potential resilience effects on medical health parameters among others.

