
Possible obstacles and limitations are as follows: (1) A prospective study design bears the risk of a higher drop-out, especially of those who show higher levels of emotional distress [76]. To minimize the risk of a selective drop-out, participants receive a monetary incentive, which will likely increase study adherence. In addition, we have established regular contact via short text messages over the course of the observation period to reinforce committment to the study [77]. (2) The Covid-19 pandemic and particularly the first lockdown had an influence on our recruiting success because medical appointments were postponed or patients did not show up, some medical facilities had to take on other medical care tasks, etc. Furthermore, the Covid-19 pandemic posed an additional coping challenge for youths and will most likely have an impact on their psychosocial adaptation, as the pandemic elicits life events with uncertainty, ambiguity, and loss of control, each of which is known to trigger psychosocial distress, including anxiety, depression, and anger [78]. Especially individuals with CCs might experience more emotional distress than their “healthy” peers, as they are at high risk for severe Covid-19 disease progress [79]. It can be assumed that intra- and interpersonal resiliency factors also have a major influence on the adaptation when dealing with this situation. Therefore, we decided to monitor possible Covid-19 pandemic effects by implementing an additional Covid-19 assessment. This will allow us to observe coping with a stressful life event and to examine its unique influence.

In conclusion, our study will contribute to a deeper understanding of the dynamic process of psychosocial adaptation when facing a CC. Based on the empirical data of this longitudinal observational study, tailored resource-based interventions supporting a positive adaptation in youths with a CC can be developed. Such intervention approaches are not only suitable for helping those adolescents who already face adjustment problems. They can also be applied to prevent them from developing in the first place.

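### The plan asks for at least 200 per group and claims near-equal groups, but Table 1 allows at most 153 conspicuous participants within the planned N = 450

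*Protocol article*

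**What the plan says.** The Abstract states the overall plan: "We plan to consecutively recruit *N* = 450 adolescents (12–21 years) from three German patient registries". The Sample size section says that the multi-group latent structural equation model sets the number, with screening status as the grouping factor. It cites a rule of thumb of not fewer than 200, notes that computation should be possible above 100, and concludes that "a total sample size of 400 should be sufficient". It then gives 100 as the minimum for each group, and the following sentence is "Therefore, at least 200 participants in each group should be achieved". It expects more inconspicuous than conspicuous participants, says of group differences in covariates that "we will consider appropriate matching procedures", and raises the inconspicuous target to 250.

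Table 1, under Recruitment, reports the preliminary sample: 426 in total, 297 inconspicuous and 129 conspicuous. Recruitment is described as consecutive and ongoing.

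Point (5) of the Discussion presents group size as a strength: "By ensuring that both subsamples are nearly comparable with respect to the sample size", the resource profiles can be compared, and "the sample sizes will be large enough for applying multi-group comparisons over time". The first limitation in the Discussion says that a prospective design "bears the risk of a higher drop-out, especially of those who show higher levels of emotional distress".

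**The concern.** Two things do not fit together. First, the section gives two per-group minima, 100 and 200, and presents the second as a consequence of the first. A reader cannot tell which one the study must meet. Second, the higher minimum and the balance claim disagree with the counts printed in the same article.

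This matters because the comparison of the two groups is the analysis from which the sample size was derived. The smaller group limits its precision, and that is also the group in which the article expects more drop-out. If the article tells readers that the groups are near equal and large enough, a multi-group analysis that finds no difference is more easily read as showing that the same processes operate in both groups.

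**Working it through.** **Inputs.** Planned total 450 (Abstract). Sufficient total 400, per-group figures 100 and 200, inconspicuous target 250 (Sample size). Recruited: 297 inconspicuous and 129 conspicuous (Table 1). The article gives no drop-out rate, power, significance level or effect size, so no power formula can be reproduced.

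**1. The plan's own totals.** 200 + 200 = 400, and 200 + 250 = 450. Both stated totals are reproduced, and both use 200 for the conspicuous group. With 100 per group the minimum total would be 200. The planned total therefore rests on the 200.

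**2. Position in Table 1.** 297 + 129 = 426. The conspicuous share is 129/426 = 30.3%. The ratio is 297/129 = 2.30:1, against a planned 250/200 = 1.25:1. The inconspicuous group is 297 − 250 = 47 above its target, and the conspicuous group is 200 − 129 = 71 below.

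**3. What N = 450 can still deliver.** Places left: 450 − 426 = 24, fewer than the 71 needed.

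| Case at N = 450 | Conspicuous | Inconspicuous | Ratio |
|---|---|---|---|
| All 24 places conspicuous | 129 + 24 = 153 | 297 | 1.94:1 |
| Observed share continues | 129 + 24 × 0.303 ≈ 136 | ≈ 314 | 2.30:1 |

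The most favourable case is 200 − 153 = 47 short.

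**4. Total needed for 200 conspicuous.** If only conspicuous participants are added: 426 + 71 = 497. If consecutive recruitment continues at the observed share: 200/0.3028 = 660.5, so 661.

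**5. Loss before T2.** The rates here are assumptions. For 10%, 20% and 30% loss, 129 becomes about 116, 103 and 90. Fewer than 100 conspicuous participants are observed at T2 once loss exceeds 1 − 100/129 = 22.5%; starting from 136 or 153 the limits are 26.5% and 34.6%. To observe 200 at T2, 223, 250 or 286 would have to be recruited.

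**6. Matching.** If matching were 1:1 without replacement, the analysed sample could not exceed twice the conspicuous count: 2 × 129 = 258 at present and 2 × 153 = 306 at best within N = 450. Both are below the plan's 400.

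**The case against.** The strongest reply is that Table 1 is a preliminary count in an ongoing study. The article gives 450 as a plan and states no stopping rule. The inconspicuous group has already passed its target, so the targets are not acting as caps. This stands: a reader might infer that 200 conspicuous participants can never be reached, but the documents show only that they cannot be reached within 450.

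The second reply is that the lower minimum is met, since 129 exceeds 100, and that the section openly expects imbalance. This also stands. A reader might infer that the multi-group model is invalid at this size; by the article's lower rule it is not. An expected imbalance does not, however, support a claim of near-equal groups.

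Third, the Statistical analyses section plans multiple imputation for missing data and drop-out. A reader might infer from step 5 that the floor of 100 fails. That would treat completers as the analysis sample, which is not the plan, and the loss rates are assumed. Imputation keeps participants in the model, though it does not restore all the information lost at T2.

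Fourth, matching is only to be considered, and its type is not given. Variable-ratio or full matching need not discard anyone. Step 6 is therefore a condition on one form of matching and no argument against matching as such.

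A reader might also want to put a figure on the loss of power, or to count model parameters against 129 participants. The article does not give the indicator structure, which may be left to a fuller plan, so such a count would rest on assumptions. An illustrative calculation with assumed values (R² of 0.5, correlation of 0.5 between T1 predictors, 80% power, an observed-variable formula) gives a detectable path difference of 2.80 × √[(0.5/0.75)(1/n₁ + 1/n₂)]. That is 0.22 at 200/250 against 0.24 at 129/297 without loss, and 0.24 at 160/200 against 0.27 at 103/238 with 20% loss in both. On those assumptions the shortfall alone costs 0.02 to 0.03, so it does not support a claim of a large loss of power.

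**Conclusion.** The concern holds as an inconsistency in stated size and balance. The step from 100 to 200 per group does not follow, and the planned total depends on the 200. If recruitment stops at 450, the conspicuous group ends between 129 and 153, most likely near 136, which is 47 to 71 below the stated minimum. The groups differ by a factor of about two, so the Discussion's balance claim is contradicted by Table 1. This conclusion rests only on counts in the article and on the planned total being kept; the figure of 136 also assumes that the observed share continues.

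It does not extend to saying that the target is unattainable under any recruitment, that the cross-lagged or multi-group models cannot be fitted, or that the order of modelling steps must change. The article supports none of these.

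**What to change.** 1. In Sample size, state whether 100 or 200 per group governs, and give the reason.
2. Replace the requirement of at least 200 in each group with the number that can be delivered: about 129 to 153 conspicuous participants recruited within N = 450. State an expected loss to T2 as an assumption, given the article's own warning about distressed participants. If 200 is kept, raise the planned total instead, to between about 497 and 661 depending on how the additional participants are recruited.
3. In Discussion point (5), delete the statement that the subsamples are nearly comparable in size. Qualify the statement that they are large enough for multi-group comparisons, and add that the absence of a detected group difference will not be read as equal processes.
4. If matching is used, say which kind, and note that 1:1 matching would cap the analysed sample at twice the conspicuous count (258 at present), below the plan's 400.

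The cost is a few sentences, and no extra participants unless 200 is retained. The downside is that the stated figures become less favourable.
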